## Statement of Compliance

This document is a protocol for a research project. This study will be conducted in compliance with all stipulation of this protocol, the conditions of the ethics committee approval, the NHMRC National Statement on ethical Conduct in Human Research (2007) and the Note for Guidance on Good Clinical Practice (CPMP/ICH-135/95).

## STUDY SYNOPSIS

|                               |                                                                                                                                                                                                                                                                                                                                                                                                                                                       |
|-------------------------------|-------------------------------------------------------------------------------------------------------------------------------------------------------------------------------------------------------------------------------------------------------------------------------------------------------------------------------------------------------------------------------------------------------------------------------------------------------|
| Title:                        | Pilot randomised controlled trial of probe to bone diabetic foot ulcer therapy                                                                                                                                                                                                                                                                                                                                                                        |
| Short Title:                  | PROBE-DFU Trial                                                                                                                                                                                                                                                                                                                                                                                                                                       |
| Design:                       | Multi-site, pilot, randomised controlled trial                                                                                                                                                                                                                                                                                                                                                                                                        |
| Study Centers:                | Austin Health (Melbourne, Australia)
Alfred Health (Melbourne, Australia)
Eastern Health (Melbourne, Australia)
University of Calgary Medical Centre (Alberta, Canada)
Bendigo Health (Bendigo, Australia) – Satellite Site                                                                                                                                                                                                               |
| Hospital:                     | Austin Hospital
Alfred Hospital
Box Hill Hospital
Bendigo Hospital Clinical Services Campus                                                                                                                                                                                                                                                                                                                                                  |
| Study Question:               | In patients with diabetic foot ulcers that probe to bone without X-ray changes of osteomyelitis, is short course antibiotic therapy feasible and safe compared to longer course antibiotic therapy?                                                                                                                                                                                                                                                   |
| Intervention                  | 2 weeks antibiotic therapy from date of randomisation                                                                                                                                                                                                                                                                                                                                                                                                 |
| Control                       | 6 weeks antibiotic therapy from date of randomisation                                                                                                                                                                                                                                                                                                                                                                                                 |
| Feasibility outcomes          | -Eligibility to recruitment ratio
-Retention rate
-Adherence to protocol                                                                                                                                                                                                                                                                                                                                                                        |
| Safety outcomes               | -SAEs, including all-cause mortality
-Antibiotic-associated adverse event
- Clostridioides difficile associated diarrhoea
-Number of hospital readmissions during the follow-up period related to treatment of diabetic foot infection or complications arising                                                                                                                                                                       |
| Exploratory clinical outcomes | -Recurrence of infection at same or contiguous site, diagnosed clinically or radiologically requiring administration of multiple (>1) doses of antibiotic therapy within the follow-up period
-Recurrence or persistence of infection at same or contiguous site requiring surgical debridement/amputation within the follow-up period
-Persistence of infection at same site requiring continuation of antibiotics beyond the planned duration |
| Inclusion Criteria:           | -Adult patient (≥18 years) with diabetic foot ulcer
-Ulcer with positive probe-to-bone test
-X-ray performed within 72 hours of enrollment demonstrating no changes suggestive of osteomyelitis at the site of the ulcer by the reporting radiologist-Willing and able to consent                                                                                                                                                               |
| Exclusion Criteria:           | -Patient <18 years of age
-Ulcer with negative probe-to-bone test
-X-ray demonstrating changes consistent with osteomyelitis at the site of the ulcer at initial visit
-Systemic antimicrobial therapy for >7 days within last 30 days prior to enrollment                                                                                                                                                                                   |

|                             |                                                                                                                                                                                                                                                                                                                                                                                                                                               |
|-----------------------------|-----------------------------------------------------------------------------------------------------------------------------------------------------------------------------------------------------------------------------------------------------------------------------------------------------------------------------------------------------------------------------------------------------------------------------------------------|
|                             | 
 
-Systemic signs of sepsis based on SIRS criteria
 
-Initial surgical therapy deemed more appropriate than medical management alone of diabetic foot infection
 
-Known pregnancy
 
                                                                                                                                                                                              |
| Number of Planned Subjects: | 120 participants (60 in intervention group, 60 in control group)                                                                                                                                                                                                                                                                                                                                                                              |
| Investigational product:    | Nil                                                                                                                                                                                                                                                                                                                                                                                                                                           |
| Safety considerations:      | Serious adverse events (SAE) will be recorded as per definition                                                                                                                                                                                                                                                                                                                                                                               |
| Statistical Methods:        | 
 
-Feasibility outcomes presented as percentage with 95% confidence intervals
 
-Exploratory clinical outcomes and safety outcome presented as risk difference with 95% confidence intervals.
 
-Amount and pattern of missing data will be explored
 
-Data analysis will be conducted on an intention-to-treat principle alongside an additional per-protocol analysis
 
 |
| Subgroups:                  | Immunocompromised                                                                                                                                                                                                                                                                                                                                                                                                                             |

## Glossary of abbreviations and terms

| Abbreviation or term                                 | Description                                                                                                                                                                                                                                                                                                                             |
|------------------------------------------------------|-----------------------------------------------------------------------------------------------------------------------------------------------------------------------------------------------------------------------------------------------------------------------------------------------------------------------------------------|
| Antibiotic-associated adverse event                  | Any unexpected adverse reaction to a prescribed antibiotic (e.g. allergic reaction, end-organ toxic effect, gastrointestinal intolerance, haematological abnormalities, etc)                                                                                                                                                            |
| Clostridioides difficile associated diarrhoea | Diarrhoea (with or without colitis) demonstrated to be caused by infection from the bacterium Clostridioides difficile , generally associated with recent antibiotic use                                                                                                                                                         |
| Diabetic foot infection                              | Soft tissue and/or bone infection of the foot in the setting of diabetes and associated neuropathy and/or peripheral arterial disease                                                                                                                                                                                                   |
| Immunosuppression                                    | Medical condition or iatrogenic cause resulting in reduction of immune response (e.g. solid organ tumour, transplant recipient, human immunodeficiency virus infection, splenectomy/functional asplenia, immunosuppressing medications)                                                                                                 |
| OM                                                   | Osteomyelitis (i.e. infection of bone tissue)                                                                                                                                                                                                                                                                                           |
| Primary site                                         | Under the Teletrials Model, the Primary Site coordinates the trial across a cluster to enhance participant reach, recruitment and management. The Principal Investigator located at the Primary Site has full responsibility for conducting the clinical trial at their site and any Satellite Site within their cluster under ICH GCP. |
| PTB                                                  | Probe-to-bone test. A bedside clinical test performed by a trained clinician (podiatrist or experienced doctor) where a blunt metal                                                                                                                                                                                                     |

|                       |                                                                                                                                                                                                                                                                                                                                                                       |
|-----------------------|-----------------------------------------------------------------------------------------------------------------------------------------------------------------------------------------------------------------------------------------------------------------------------------------------------------------------------------------------------------------------|
|                       | probe is inserted into an ulcer to palpate for any hard bone.                                                                                                                                                                                                                                                                                                         |
| Satellite site        | A Satellite Site is located in a geographically separate health facility and trial activities are delegated by the Primary Site (clinical trial site) to the Satellite Site, to enable performance of activities associated with the conduct of a clinical trial at the Satellite Site and to support trial accessibility of remote participants to a clinical trial. |
| Serious adverse event | Any adverse occurrence during the trial that is thought to result in death, life-threatening event, requires hospitalisation or lengthening of hospitalisation, or results in permanent/significant disability                                                                                                                                                        |
| Teletrial             | A teletrial uses telehealth technology to communicate between the Primary Site and Satellite Site/s and enables delivery of aspects of a clinical trial closer to home for patients, particularly in regional, rural and remote locations.                                                                                                                            |

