### 2.3 Outcomes

#### **Primary Outcome measures**

The primary endpoint will be feasibility and safety of the trial.

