### 3.9 Follow up assessment data

Follow up will be at Day 14 ( $\pm$  2 days), day 42 ( $\pm$  2 days) and day 90 ( $\pm$  5 days) from date of recruitment. Data collected at these assessments will include:

- Attendance at follow up
- Mode of follow up assessment (i.e. in-person, telehealth (video) or telephone consult)
- Medication-related adverse events (see Appendix 3)
- Medication adherence assessment (see Appendix 4)
- Ulcer size
- Wlfl score
- Serum biomarkers (total peripheral white cell count, serum C-reactive protein)
- Changes to antibiotic therapy

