### Appendix 3 – Medication adverse event assessment

| Adverse event category  | Adverse event and definition                                                                                                                                                                                                                                                             | Present at review (Yes/No) | Details |
|-------------------------|------------------------------------------------------------------------------------------------------------------------------------------------------------------------------------------------------------------------------------------------------------------------------------------|----------------------------|---------|
| Gastrointestinal | Diarrhoea: >3 loose stools per day associated with antibiotic administration in the absence of laxative or pre-existing enteritis                                                                                                                                                        |                            |         |
|                         | Nausea and vomiting: associated with antibiotic administration, in the absence of alternate explanation                                                                                                                                                                                  |                            |         |
| Haematologic     | Anaemia: Hb<100g/L                                                                                                                                                                                                                                                                       |                            |         |
|                         | Leukopenia: WCC < 4.0 x 10  /L                                                                                                                                                                                                                                               |                            |         |

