|                         | Thrombocytopenia: platelet count <150 *10  /L                                                                                                                                                                                                                                |                            |         |
| Hepatobiliary    | Cholestasis: total bilirubin >21µmol/L                                                                                                                                                                                                                                                   |                            |         |
|                         | Transaminitis: AST or ALT >3 times patient's baseline                                                                                                                                                                                                                                    |                            |         |
| Renal            | Increase in serum creatinine >1.5 times patient's baseline                                                                                                                                                                                                                               |                            |         |
| Neurologic       | Altered mental status compared to patient's baseline                                                                                                                                                                                                                                     |                            |         |
|                         | Peripheral neuropathy                                                                                                                                                                                                                                                                    |                            |         |
|                         | Seizures                                                                                                                                                                                                                                                                                 |                            |         |

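### The antibiotic-associated adverse event outcome is defined one way in the glossary and collected another way in Appendix 3, so its between-arm risk difference may be distorted

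*Protocol*

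**What the plan says.** Section 2.3 states that "The primary endpoint will be feasibility and safety of the trial" and lists antibiotic-associated adverse event among four safety outcomes. Section 6.2 reports safety outcomes as risk differences with 95% confidence intervals.

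The glossary defines the event as "Any unexpected adverse reaction to a prescribed antibiotic" and gives as examples "allergic reaction, end-organ toxic effect, gastrointestinal intolerance, haematological abnormalities, etc".

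Section 3.9 collects medication-related adverse events at days 14, 42 and 90 and refers to Appendix 3. That form lists events by organ system. Each row has an answer column headed "Present at review (Yes/No" and a free-text details column. There is no field for onset date, stop date or occurrence since the previous visit.

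In the neurologic block, one row reads only "Peripheral neuropathy". The glossary describes diabetic foot infection as arising "in the setting of diabetes and associated neuropathy and/or peripheral arterial disease".

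The hepatobiliary block includes "Transaminitis: AST or ALT >3 times" the patient's baseline. The blood tests listed for follow-up are "Serum biomarkers (total peripheral white cell count, serum C-reactive protein"; section 3.7 and Appendix 2 list the same two at baseline.

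**The concern.** The glossary and the form can count different events. An investigator who applies the word 'unexpected' could leave out a known side effect that another records because it has a row on the form.

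The form, read literally, is a snapshot. A rash or diarrhoea that begins and ends between visits has no dedicated field. The arms differ in how much treatment time lies between visits, so the loss need not be equal.

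Some rows can be positive for reasons that predate the trial, and others need tests that the protocol does not list. The first adds events unrelated to treatment. The second makes detection depend on who happens to be tested.

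At stake is a safety comparison inside the primary endpoint. Section 6.1 also intends the pilot to supply local estimates for planning later trials, so a distorted difference would carry forward.

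**Working it through.** **The plan's own figure.** There is none for this outcome. The only stated precision, a confidence interval below 20%, concerns feasibility percentages. It reproduces on the whole sample: 2 × 1.96 × √(0.5 × 0.5 / 120) = 17.9 points. It does not bear on adverse events.

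**1. Definition against form.** The glossary qualifier is 'unexpected'. Its examples include gastrointestinal intolerance and allergic reaction. Appendix 3 has rows for diarrhoea, nausea and vomiting, and rash, with no expectedness test. The three cannot all be applied together.

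**2. Visit gaps against exposure.** Visits are at days 14, 42 and 90, so the gaps are 42 − 14 = 28 and 90 − 42 = 48 days. Planned exposure is 14 or 42 days. (The synopsis counts the course from randomisation, sections 3.3 and 3.4 from the index X-ray; nominal durations are used here.) The 28-day gap is therefore on-treatment only in the 6-week arm.

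**3. Baseline condition, row by row (Appendix 3).**

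| Row | Judged against baseline? | Test listed in 3.7, 3.9 or Appendix 2? |
|---|---|---|
| Altered mental status | yes | not a blood test |
| Peripheral neuropathy | no | not a blood test |
| AST/ALT | yes | no |
| Creatinine | yes | no |
| Bilirubin | no | no |
| Haemoglobin | no | no |
| Platelets | no | no |
| White cell count | no | yes |

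Appendix 1 schedules blood tests at days 0, 14 and 42 without naming analytes.

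**4. Illustration of incomplete capture. All inputs are assumptions; the documents give none.** Take a constant hazard λ of a first reaction while on drug, exponential duration with mean m days, and a reaction counted only if ongoing at a visit. Day 14 detection is the same in both arms, so the recorded difference is the day 42 term:

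RD recorded = λ/(1/m − λ) × [e^(−42λ) − e^(−14λ) × e^(−28/m)]

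With a 10% risk per 14 days, λ = −ln(0.9)/14 = 0.00753. Full-capture risks are 10.0% and 1 − 0.9³ = 27.1%, a difference of 17.1 points.

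- m = 3: 0.0231 × (0.729 − 0.9 × 0.0001) = 1.7 points, 10% of 17.1
- m = 7: 0.0556 × (0.729 − 0.9 × 0.0183) = 4.0 points, 23%
- m = 14: 0.1178 × (0.729 − 0.9 × 0.1353) = 7.2 points, 42%

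At 20% per 14 days the full difference is 0.800 − 0.512 = 28.8 points, and the same formula gives 2.6, 6.2 and 11.6 points.

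**5. Illustration of false positives, again with assumed inputs.** If a share q in each arm is positive whatever the treatment, the observed risk is q + (1 − q)p, so the difference is multiplied by (1 − q). From 17.1 points: 15.4 at q = 10%, 12.0 at 30%, 8.6 at 50%, 5.1 at 70%.

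**6. Unequal testing.** If a share r would show an abnormal value in both arms, and shares t₆ and t₂ are tested in the 6-week and 2-week arms, the rows add r × (t₆ − t₂) to the difference with no drug effect at all. More testing in the longer arm widens the difference. The documents give neither r nor the testing rates.

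**The case against.** A reader might infer three stronger things.

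**That ordinary reactions are missed.** The documents do not support this. The glossary names such reactions as examples and Appendix 3 has rows for them. What stands is the contradiction, which lets investigators count differently.

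**That pre-existing neuropathy is counted.** The glossary requires a reaction to a prescribed antibiotic, section 3.9 speaks of medication-related events, and Appendix 2 records microvascular complications at baseline. An investigator could exclude old neuropathy on those grounds. What stands is that the row applies no such test, although the diarrhoea and nausea rows carry an attribution and neighbouring rows a baseline comparison.

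**That a known share of the arm difference is lost.** No document figure supports any share. Reactions lasting 28 days or more would not be lost between days 14 and 42. If onsets cluster in the first two weeks, both the true difference and the differential loss shrink. Unequal laboratory testing works in the opposite direction.

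The snapshot reading also rests on a column heading. Section 3.9 states no such limit, and the same column covers seizures and anaphylaxis, which a literal snapshot would rarely catch. The details column, the record of antibiotic changes and the side-effect reason in Appendix 4 may recover some events; serious events and *C. difficile* diarrhoea are separate outcomes. This weakens the claim of certain loss. It does not supply a question about the interval since the last visit.

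Finally, this is a pilot with 60 per arm and no stated test for this outcome. At an assumed 0.5% per day, the risks are 1 − e^(−0.07) = 6.8% and 1 − e^(−0.21) = 18.9%. The difference is 12.2 points, with a 95% interval of about ±1.96 × √(0.068 × 0.932/60 + 0.189 × 0.811/60) = ±12 points even with perfect capture. That limits the consequence and the severity. It does not excuse a correctable bias in an estimate within the primary endpoint.

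**Conclusion.** The point holds as inconsistent definition and capture of a safety outcome within the primary endpoint. The conflict over 'unexpected', the absence of a question covering the interval between visits, the missing baseline conditions and the unlisted laboratory tests can all be read from the protocol without assumptions.

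The effect on the risk difference is inference. It would probably move towards zero if reactions accrue with days on drug, if short-lived reactions go unrecorded, and if false positives are equal between arms. It could move away from zero if the longer arm has more laboratory tests. The percentages in the working show only how sensitive the result is; they do not estimate the bias in this trial, and the net direction cannot be fixed from the documents. An analysis plan could settle the counting rules, but it could not recover information that the form never asked for.

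This should be fixed, but it does not invalidate the trial.

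**What to change.** - Delete 'unexpected' from the glossary definition, so that it agrees with its examples and with Appendix 3.
- Change the Appendix 3 answer column to: Occurred since last review (Yes/No), with onset and stop dates.
- Complete Appendix 3 at day 0 as well, and count only items that are new or worse than at day 0.
- Either run AST/ALT, creatinine, bilirubin, haemoglobin and platelets on the draws already scheduled at days 0, 14 and 42 and list them in sections 3.7 and 3.9, or leave those rows out of the between-arm comparison.

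The cost is one word in the glossary, a slightly longer form, one additional form at day 0 and, if the analytes are run, a small laboratory cost. No treatment rule changes.
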